## Abstract

**Background:**

Older Australians are high consumers of complementary and alternative medicines (CM). To help older people to take an active role in their health, we will develop and evaluate a novel educational intervention to support decision self-efficacy, and improve health literacy skills.

**Methods:**

The primary hypothesis is that participants receiving a web/DVD plus booklet intervention compared with a booklet-only group will demonstrate an increase in decision self-efficacy. This study is a randomised controlled trial. One hundred and sixty-eight people aged 65 years and older will be recruited from community settings comprising retirement villages and community groups, based in Sydney, Australia. Participants will be randomly allocated to either the education intervention delivered by the Internet or a DVD plus booklet versus a control group (booklet only). The primary outcome measure is CM decision self-efficacy. Secondary outcomes are health literacy, knowledge and attitudes, and change in health-seeking behaviour. Participants’ views on the ease of using the resources, the length of the modules, the amount of information, and participant understanding of the modules will be assessed. Outcomes will be collected on completion of the intervention at 3 weeks, and at a 2-month follow up from trial entry.

**Discussion:**

This trial has the potential to improve CM health literacy in older Australians. There are no educational resources designed to support decision self-efficacy and improve health literacy amongst older people related to CM.

**Trial registration:**

Australian New Zealand Clinical Trials Registry (ANZCTR), ACTRN12616000135415. Registered on 5 February 2016.

**Electronic supplementary material:**

The online version of this article (doi:10.1186/s13063-017-2182-2) contains supplementary material, which is available to authorized users.

## Background

More than three million Australians (14% of the population) are aged over 65 years [1]. Studies indicate seniors take an active role in their health care to improve their health and wellbeing [2], and there is growing evidence that seniors are high users of complementary medicines (CMs). A survey of older Australians found 58% of those aged over 65 years have used at least one of 17 common CM modalities in a previous 12-month period, and 65% of these had visited a CM provider [3]. The Australian Longitudinal Study of Aging, an ongoing prospective study of the older population, demonstrated the prevalence of CM utilisation to have increased over time, from 17% in 2000–2001 to 35% in the 2003–2004 period [4]. CM is generally used to treat a wide range of chronic health complaints that become increasingly common with age [5], particularly musculo-skeletal conditions and pain [6], and anxiety or depression [7]. CM users report significant benefits to both their physical and mental health from CM [8, 9], and that CM is highly valued by encouraging individuals to participate in their health [10].

To be health literate implies having a range of skills and knowledge about health and health care, including the ability to find, understand, interpret, and communicate health information, seek appropriate care, and make critical health decisions [11]. Systematic reviews have concluded that low levels of health literacy are associated with poorer treatment outcomes, including poor compliance with medication, increased admissions to emergency departments, lower ability to interpret labels and health messages, reduced health status, and increased mortality among the elderly [12]. The ability to obtain reliable health information is important to all populations but particularly older people. Reports indicate an increasing number of older people are seeking information on the Internet [13], yet remain unaware of how to identify quality information to guide their use of this information.

There has been significant discussion in the literature about what constitutes health literacy and how to measure it. The health literacy Ophelia Project undertaken at Deakin University, Australia, identified nine concepts of health literacy [14]. These include having sufficient information to manage health, social support for health, skills to appraise health information, ability to engage with healthcare providers, capacity to navigate the healthcare system, ability to find good health information, and sufficient understanding of health information to know what to do with it.

Complementary medicine may offer a way for older people to cope with their ill health, or to engage in maintaining their health; however, this assumes good health literacy skills. There has been little research examining the decision self-efficacy of CM users and their levels of health literacy. This could be of particular concern due to the use of CM without adequate supervision by a qualified health practitioner, and a higher prevalence of polypharmacy arising from the treatment of complex chronic health conditions [15]. Seniors may also be more susceptible to medication sensitivity due to less optimal organ function associated with aging [15–17]. Together, these concerns may increase the risk of potential CM-drug interactions. In the Australian community, the prevalence of serious adverse reactions to CM is relatively low compared to pharmaceutical medications [18]; however, mild reactions are common. A retrospective review of previously collected health data identified that 15% of 5052 participants used CM and 5.8% were identified as having a significant risk of an adverse reaction [19]. These risks were linked to garlic and ginkgo biloba and their interactions with drugs affecting blood coagulation, such as aspirin and warfarin, which, represented 95% of the (potential) significant interactions identified. Other high-risk natural product and drug combinations identified as potentially dangerous include ginseng and warfarin, and St John’s wort used along with digoxin.

This risk of interactions is further complicated by limited disclosure of CM use between consumers and their healthcare providers. Non-disclosure rates to healthcare providers among those using CM have been reported to be as high as 71% [18, 20]. There are multiple reasons for non-disclosure including the individual forgetting to mention CM use, disclosure not being seen as relevant, the doctor not asking about CM use, and the doctor not respecting the value of CM [20]. Disclosure and communication about CM is essential for achieving optimal treatment outcomes.

To explore these issues, we recently completed a two-phase, sequential, mixed-method study incorporating quantitative and qualitative methods to examine CM health literacy in a population of older Australians living in retirement villages [21]. We found older Australians using CM were making decisions regarding managing their own health and self-care [21]. Our primary findings suggest this population demonstrate differing competencies relating to health literacy. We identified three scales where older adults scored low including *navigating the health care system, an ability to find good information*, and *appraisal of health information*. Interpretation of these scales suggests that some participants were unable to understand most health information and were confused when they were presented with conflicting information. We found that these seniors were also unable to access health information when required, they were frequently dependent on others to offer information, were unable to advocate on their own behalf, and struggled to find someone who could help them to use the healthcare system to address their health needs.

There are few programmes that have addressed the specific health literacy needs of older people. A pilot health literacy programme that aimed to build health information literacy skills found that following literacy workshops, participants were empowered to ask questions and reported greater success with finding health information online [22].

Based on our study findings we have developed an educational intervention to increase older adults’ skills and ability to identify good and reliable sources of CM information, resolve conflicting information, and access a diverse range of current CM information sources that can be used to guide their CM decisions with their healthcare providers. The aim of this study is to determine the effectiveness of the CM educational intervention to increase older adults’ health literacy and decision self-efficacy. Improved CM health literacy will enhance appropriate use of health services and ultimately enable older Australians to engage in taking an active role in their health, and reducing the potential for adverse health outcomes.

## Methods/designs

The primary hypothesis is that participants receiving a web/DVD plus booklet intervention compared with a booklet-only group will demonstrate an increase in decision self-efficacy. The secondary hypotheses are that participants receiving a web/DVD plus booklet intervention compared with a booklet-only group will demonstrate an increase in health literacy, communication skill, and change in health-seeking behaviour.

### Study design

This study (see Fig. 1) is a parallel, randomized, controlled trial of a CM education intervention delivered online (using a purpose built website) or DVD plus booklet versus a control group (booklet only) to examine the effect on decision self-efficacy, health literacy, perception of risk, and health-seeking behavior, on completion of the intervention at 3 weeks, and at 2-month follow up from trial entry. Full details of reporting of the trial protocol items can be found in the “Standard protocol items: recommendation for interventional trials” (SPIRIT) checklist (please see Additional file 1).

**Fig. 1 Fig1:**
[figure not shown]
Schematic illustration of the research design

### Trial setting

We will recruit participants from a community setting comprising retirement villages and community groups, based in Sydney, Australia. In Australia, a retirement village is made up of housing for people aged over 55 years who are able to live independently. Many of these villages offer some healthcare services, leisure facilities, and social clubs. The village provides smaller, manageable housing, supportive of the changing needs of older people. In this setting, we will contact the managers of the retirement villages to describe the study and seek permission to come and promote the study to residents. We will also recruit from various community groups, including senior citizen clubs, associations and referrals from study participants.

### Study population

The study population will comprise men and women aged 65 years and older, with access to the Internet or a DVD player or computer, who will provide informed consent for participation in the study. Exclusion criteria include being unable to communicate in English or living in a long-term care facility.

### Randomisation and blinding

The randomisation sequence was computer generated by an online randomisation service by Sealed Envelope randomisation service, Ltd 2016 (https://www.sealedenvelope.com/), with the codes concealed in sealed, opaque envelopes. Participants will be randomised in a 1:1 ratio, in blocks of eight to either group 1: web/DVD resource plus booklet, or group 2: control booklet only (see Fig. 1). Participants are not blind to their group allocation; however, the study analyst will be blind during analysis, and the codes will be broken following statistical analysis. The trial co-ordinator was not blind to study group.

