### Sample size calculation

The sample size was calculated using GPower, and was based on “sample size effect” drawn from published data [23]. It was estimated that a moderate effect size would be obtained (i.e. Cohen *D* = 0.5) for the primary endpoint only, with improved decision self-efficacy between groups at the end of the 3-week intervention. With the alpha value set at 0.05 and power at 0.8 (i.e. 80% chance that the expected effect size would be significant), a minimum sample size of 64 per group, with rounding to 70 per group was estimated. Allowing for 20% attrition, a total sample size of 168 participants was required for this trial (i.e. 84 per group).

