### Procedure for the trial

Following completion of the pilot and minor modification to the resources, recruitment for the main trial commenced in July 2016. Recruitment will be undertaken at all interested retirement villages. Study promotion will involve letter box drops, and promotional talks by the investigators and the trial co-ordinator. At these visits, following a promotional study presentation, expressions of interests will be gathered and participant information and consent forms made available. A mutually convenient time will be made to obtain informed consent and to complete baseline questionnaires.

Following randomisation, the trial co-ordinator will meet with each participant to ensure they are able to access the website using the password and to navigate the modules, or ensure navigation with the DVD is satisfactory. To minimise attrition, all groups will receive a phone call mid-way through the intervention to ensure they are continuing to access the resources and address any difficulties. Primary and secondary outcome data will be collected at baseline, at the end of the intervention and at two months from trial entry. At trial entry we will collect baseline data on socio-demographic (age, gender, place of birth, education status, employment status, ethnicity, English skills, Medicare and private health insurance) and health characteristics, health behaviour, and lifestyle including CM use, sources of information, Internet skills, health literacy status, and decision-making (Fig. 2: SPIRIT figure).

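### One fixed block size of eight in an open-label trial leaves up to 20% of allocations deducible in advance, if recruiting staff know the block size and track past allocations

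*Protocol article*

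**What the plan says.** The section Randomisation and blinding gives the scheme: "Participants will be randomised in a 1:1 ratio, in blocks of eight to either group 1". It mentions neither varying block sizes nor stratification. The sequence came from an online randomisation service, "with the codes concealed in sealed, opaque envelopes". On masking it says "Participants are not blind to their group allocation" and "The trial co-ordinator was not blind to study group"; only the analyst is blind.

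The section Procedure for the trial describes the co-ordinator's part. Before entry: "Study promotion will involve letter box drops, and promotional talks by the investigators and the trial co-ordinator". Expressions of interest are collected after these presentations, and an appointment is then made for consent and the baseline questionnaires. After entry: "Following randomisation, the trial co-ordinator will meet with each participant to ensure they are able to access the website". All groups also receive a telephone call half-way through the intervention.

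The article does not say who takes consent, who holds or opens the envelopes, or whether the block size was kept from the people who recruit.

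**The concern.** In an open-label trial, past allocations become visible as the trial runs. With one fixed block size, that history can determine the next allocation, and an opaque envelope cannot prevent this. The co-ordinator has a hand in promotion before entry and sees allocations after it. Even if the set-up meeting concerns only web/DVD participants, the others are controls by elimination.

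Someone who can foresee the next arm can influence who is approached or booked next. Entry order has some play here, because appointments are arranged individually and recruits come from villages, clubs and referrals by participants. The arms could then differ in motivation or confidence before any intervention is delivered. The primary outcome is self-reported decision self-efficacy from participants who know their arm, so selection bias would come on top of any response bias.

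**Working it through.** **Inputs.** Block size 8, ratio 1:1 (four places per arm) and envelope concealment, from Randomisation and blinding. Total 168, from Sample size calculation. The article gives no figure for predictability, so there is none to reproduce. The total fits the scheme exactly: 168 / 8 = 21 complete blocks.

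**Assumptions.** The observer knows the block size and sees every earlier allocation in order, and there is a single list.

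**Forced allocations.** A block has C(8,4) = 70 equally likely orders. A place is forced once one arm has used its four places, which means that all remaining places belong to the same arm.

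| Place in block | Probability that it is known in advance |
|---|---|
| 1st to 4th | 0 |
| 5th | 2 × C(4,4) / 70 = 2/70 = 2.9% |
| 6th | 2 × C(5,4) / 70 = 10/70 = 14.3% |
| 7th | 2 × C(6,4) / 70 = 30/70 = 42.9% |
| 8th | 70/70 = 100% |

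The sum is (2 + 10 + 30 + 70) / 70 = 112/70 = 1.6 per block. The closed form 2m/(m + 1) with m = 4 also gives 8/5 = 1.6. As a share, 1.6 / 8 = 20%. Over the trial, 21 × 1.6 = 33.6, about 34 of 168. Full enumeration agrees: 1, 2, 3 or 4 places are forced in 40, 20, 8 and 2 of the 70 orders.

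**Best guess.** Always guessing the arm with more places left, and tossing a coin at ties, gives an expected m + 2^(2m−1)/C(2m,m) − 1/2 = 4 + 128/70 − 0.5 = 5.33 correct of 8. That is 66.6%, against 50% by chance.

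**Varying block sizes.** These results are simulated lists of 168 (600 per scheme), with an observer who knows the set of sizes and the full history but not the order of the sizes.

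| Scheme | Certain in advance | Best guess correct |
|---|---|---|
| Fixed 8 | 20.0% | 66.7% |
| 4 and 8 at random | 7.5% | 68.0% |
| 4, 6 and 8 at random | 2.1% | 68.0% |
| 6, 8 and 10 at random | 1.6% | 66.3% |

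A separate run of 400 lists with sizes 4, 6 and 8 gave 2.4% and 67.9%. Varying the size removes nearly all certainty but leaves average guessing where it was.

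**What steering could do (assumed, not from the article).** Suppose every forced allocation were steered, so that those forced to the intervention sit δ SD above average on the analysed outcome and those forced to control δ SD below. The between-group bias is then 0.20δ + 0.20δ = 0.40δ. For δ from 0.1 to 0.5 this is 0.04 to 0.20 SD, against the planned effect of 0.5 SD. The article gives no basis for choosing δ.

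**The case against.** **The 20% is conditional.** A reader might infer that one allocation in five was in fact known beforehand. The article does not support that. Printing the block size in a publication does not show that recruiting staff were told it. This objection stands, and the figure is therefore an upper bound on certain foreknowledge.

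**The co-ordinator's role before entry is only partly described.** A reader might infer that the co-ordinator enrols participants and handles the envelopes. The article gives the co-ordinator a share in promotional talks and names nobody for consent or for opening envelopes. A condensed article may leave this to the full protocol. This stands too: the route to bias is possible but not documented.

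**Stratification.** The article is silent on it, which is not a statement that none was used. With several lists, the 20% still holds within each completed block, but unfinished blocks would lower the total.

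**Room to steer is limited.** Eligibility rests on age, access to a device, English and not living in long-term care, so it leaves little discretion. The primary outcome is a change in score, which takes some account of baseline differences. The article also undertakes to weigh bias when interpreting results. These points reduce the likely size of any bias, but they do not stop entry order from being influenced.

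**The remedy does not reduce guessing.** This is correct on average. What it removes is certainty, which is the stronger incentive to act.

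**Envelopes.** A reader might infer that allocation is released too early and should move online. The procedure already puts consent and baseline questionnaires before randomisation. Online release guards against tampering with envelopes, not against deduction from past allocations.

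**Conclusion.** The point holds as a conditional risk. A single block size of eight, open allocation and an unblinded co-ordinator who takes part in promotion allow up to 20% of allocations (1.6 of 8, about 34 of 168) to be certain in advance, despite sealed opaque envelopes. The bound assumes that people who influence entry know or infer the block size and follow all earlier allocations in order. The text supports access to the allocation history; it says nothing either way about knowledge of the block size.

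This is neither an error of calculation nor a contradiction, and nothing in the article shows that selection bias occurred. It is a design choice that a cheap change would improve.

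**What to change.** Generate the list with randomly varying block sizes, for example 4, 6 and 8, and withhold the sizes from everyone who recruits or takes consent. Certain foreknowledge falls from 20% to about 2%. Withholding the sizes matters as much as varying them, because an ideal tracker who knows the set of sizes still guesses right about 68% of the time. The cost is small: a different specification when the list is generated, and slightly looser balance if recruitment stops mid-block. Online release in place of envelopes is optional.

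The Trial status section says that recruitment ended in May 2017, so the list for this trial can no longer be changed. The results report can still state who took consent, who opened the envelopes and whether the block size was known to them. It can also compare baseline decision self-efficacy between the arms among the forced allocations, about 34 if all 21 blocks were filled. That check uses data already collected, but with so few participants it would detect only a large imbalance.

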### Sample size calculation

The sample size was calculated using GPower, and was based on “sample size effect” drawn from published data [23]. It was estimated that a moderate effect size would be obtained (i.e. Cohen *D* = 0.5) for the primary endpoint only, with improved decision self-efficacy between groups at the end of the 3-week intervention. With the alpha value set at 0.05 and power at 0.8 (i.e. 80% chance that the expected effect size would be significant), a minimum sample size of 64 per group, with rounding to 70 per group was estimated. Allowing for 20% attrition, a total sample size of 168 participants was required for this trial (i.e. 84 per group).

### Interventions

The educational intervention has been informed by our preliminary research [21]. The delivery of the intervention will comprise a multi-media (web/DVD) intervention, and booklet. The delivery format has been informed by findings from the Cochrane systematic review of multimedia educational interventions and offers advantages over the traditional information delivery [24]. A combination of audio with video or graphical presentation can overcome difficulties with low literacy skills [25]. Studies have also shown that learning is improved when material is presented as an audio-visual rather than visual-alone format [26, 27]. A multimedia format also has the advantage that the resources can be used at a pace that suits the user, and at a time and place that is convenient to the individual.

The education intervention comprises five modules, and includes information about CM and other self-care practices, such as exercise. The intellectual content of the intervention has been developed from the Complementary Medicine Education and Outcomes (CAMEO) research programme [28], and modified for use in the Australian context. The CAMEO resource comprises a website and booklet and was developed with links to credible and evidence-based information resources (www.cameoprogram.org/). The CAMEO resource was developed for patients with cancer; however, for this study the education resources have been adapted for use with older individuals.

